## Abstract

**Background:**

Enteral nutrition is a major pathway of nutrition for patients requiring critical care. However, it remains unclear whether intermittent or continuous feeding is the better approach, especially after nasogastric enteral nutrition via a gastric tube. Therefore, this randomized controlled clinical study was designed to observe the effects of different methods on critically ill patients.

**Methods:**

Different Feeding Methods on Gastrointestinal Function of Critical patients (DFM-GFC) is a randomized clinical study that will be performed to assess the effects of three feeding methods on critically ill patients. A total of 90 critically ill patients will be equally randomized into three groups: continuous feeding, cyclic feeding, and intermittent feeding. The patients will be administered a gastrointestinal nutrition preparation over 24 h via a gastric tube or over 16 h via an intermittent pump. The primary outcome is the mean duration (days) to reach the caloric goal in each group. Secondary outcomes include the rate of onset of gastric residual, abdominal pressure, the rate of onset pneumonia, and the proportion of individuals achieving the caloric goal. Additionally, the length of intensive care unit (ICU) stay and mortality rate at 28 days post-enrolment will be evaluated.

**Discussion:**

This study will observe the effects of different feeding methods on various parameters, such as the energy target and gastrointestinal motility, in critically ill patients to improve quality of life and reduce the case fatality rate. The purpose of this study is to explore whether there is a more effective, safer and cost-efficient feeding method for the clinical treatment of critically ill patients.

**Trial registration:**

ID: NCT04224883, ClinicalTrials.gov, registered January 9, 2020

**Supplementary Information:**

The online version contains supplementary material available at 10.1186/s13063-022-06807-7.

## Background

The majority of critical patients in the intensive care unit (ICU) require analgesia, sedation, and mechanical ventilation, as they are unable to feed themselves and need enteral nutrition (EN). EN in comparison to parenteral nutrition (PN) is being intensively explored. In the case of critically ill patients, several guidelines recommend initiating EN as soon as possible after ICU admission if the patients are able to eat [1]. These guidelines state than EN feedings via nasogastric or nasointestinal tubes may be delivered by a pump or gravity drip; however, there is no universal standard protocol.

EN can be administered through numerous methods. Three common feeding methods are continuous, intermittent, and cyclic feeding. For example, during continuous feeding, an electric infusion feeding volumetric pump delivers EN at a constant hourly rate 24 h a day. During cyclic feeding, a feeding pump administers EN in < 24 h. During intermittent feeding, EN is pumped through a volumetric pump over 20–60 min every 4–6 h [2]. In intermittent feeding, EN is delivered either by gravity drip of a volumetric pump. Intermittent feeding is not a bolus injection, which is completed in approximately 10 min by manual injection of EN, however this method is rarely used in the ICU.

Some studies suggest that although continuous feeding is well tolerated by patients, it may lead to decreased patient mobility and disrupted circadian cycles because the patient is connected to a feeding pump and the gastrointestinal tract [3, 4]. In contrast to continuous feeding, intermittent feeding is a more physiological mode of delivery. By replicating normal patterns of feeding, intermittent delivery allows a phased supply of hypertonic nutrient loads into the jejunum, which reduces the metabolic demand on the small intestine and prevents excessive accumulation of jejunal fluid [5, 6]. Nevertheless, there can be complications, such as vomiting, aspiration, and fluctuations in blood sugar levels [7]. Overall, cyclic feeding with 6-8 hours of discontinuation enhances a patient’s appetite and/or restores gastric acidity, but only a few studies have focused on this approach. Intermittent feeding at standard intervals allows for greater patient mobility and is considered a physiological method with respect to the cephalic phase of digestion and gut homeostasis [8].

The optimal method of EN delivery in ICU patients remains controversial. In 2017, a critical care nutrition expert panel identified the need for a continuous vs. intermittent feeding trial as one of the “top 10” priority studies to be carried out in the next decade [9]. Moreover, cyclic and intermittent feeding methods are less studied in China. Therefore, we have designed this randomized controlled study to compare the effects of three feeding regimens in critically ill patients. The purpose of our study is to explore whether there is a more effective, safer, and cost-efficient feeding method for critically ill patients.

## Objectives

The primary objective of the DFM-GFC study is to determine whether cyclic or intermittent feeding can extend the duration (days) of achieve caloric goal compared with continuous feeding. The secondary objective of the study is to assess whether the two feeding methods can increase the proportion of patients who achieve the caloric goal, shorten the length of stay in the ICU, and reduce the incidence of feeding complications, including the rates of onset of gastric residua and pneumonia. Abdominal pressure, motilin levels, and mortality in three groups will also be explored.

## Methods

### Design

This is a prospective randomized controlled study. There are three parallel groups: a continuous feeding group, cyclic feeding group, and intermittent feeding group. The trial protocol was written according to the Standard Protocol Items: Recommendations for Interventional Trials Statement (SPIRIT). A SPIRIT table is provided in Fig. 1, and a SPIRIT checklist is included in Additional file 1.

**Fig. 1 Fig1:**
[figure not shown]
SPIRIT schedule of enrolment, interventions, and assessments. Liver function includes alanine aminotransferase (U/L), aspartate aminotransferase (U/L), total bilirubin (μmol/L), direct bilirubin (μmol/L), and albumin (g/L). Renal function includes blood creatinine (mmol/L) and urea (mmol/L)

### Allocation and blinding

A random number table generated by SPSS 20.0 software (IBM Co., Armonk, NY, USA), using the randomization method, will be employed to assign the participants to each group at a ratio of 1:1:1. Patients will be enrolled during allocation according to the sequence of ICU admission. For masking, random sequences and group assignments will be sealed in opaque envelopes. As this study is a comparative assessment of treatment modalities, blinding will not be feasible. Masking related to the participant treatment arm allocation and to the treatment team for the baseline and follow-up assessments will be applied for the assessment team, data manager, and statistician.

### Participants

Three separate cohorts of patients admitted to the ICU of Guangdong Hospital of Chinese Medicine who satisfy the inclusion/exclusion criteria outlined below will be recruited for this study. Before recruitment, the research team will prepare and publish recruitment advertisements and hold consultation meetings with doctors specializing in critical care in the hospital.

### Inclusion criteria

The following inclusion criteria will be applied: participants (1) aged 18–80 years, (2) with Acute Physiology and Chronic Health Evaluation (APACHE)-II ≥ 15 [10], (3) in whom EN can be used after evaluation, (4) with an expected ICU stay of > 48 h, and (5) patients or family members signed informed consent.

### Exclusion criteria

The following exclusion criteria will be applied: participants (1) required to fast clinically, such as those with digestive tract perforation, bleeding, or gastrointestinal tract surgery; (2) who are allergic to EN preparations; (3) have unstable hemodynamics; (4) who are unwilling to participate in the trial or cannot cooperate with the treatment, and (5) who are pregnant and lactating.

### Interventions

Patients will be randomized into three arms: a continuous feeding group, cyclic feeding group, and intermittent feeding group. In the continuous group, an electric infusion feeding pump will deliver EN at a constant hourly rate of 24 h/day. The critical patients who are randomized to the cyclic feeding group will receive the EN preparation for 16 h via continuous pumping through the stomach tube every day. The initial pumping speed of the two groups will be calculated as the average pumping volume of the total enteral nutrition in 1 day. For example, if the total daily intake is 1200 mL, the initial pumping speed of the continuous group will be 50 mL/h, which of cyclic is 75 mL/h. The gastric residual volumes (GRV) will be checked every 4 h. If it is not tolerable, the pumping speed will be reduced by half of the original speed. Feeding intolerance will be defined as GRV > 250 mL; EN will be stopped and reassessed after 4 hours if GRV > 500 mL. The critical patients who are randomized to the intermittent feeding group will be administered the EN preparation through four meals every day (at 08:00, 12:00, 18:00, and 22:00). In the intermittent group, the daily amount of feeding will be divided into four meals, and each meal will be pumped through the stomach tube within 60 min or 120 min. The following EN preparation pumping scheme will be used. If the volume of each meal is less than or equal to 250 mL (≤ 250 mL), it will be delivered within 60 min; if the volume is greater than 250 mL (> 250 mL), it will be delivered within 120 min. If the total daily intake is 1200 mL, the initial pumping speed will be 150 mL/h. GRV will be checked before each intermittent feeding. If it is not tolerable, the pumping speed will be reduced by half of the original speed. If GRV > 500 mL, EN will be stopped and reassessed after 4 hours. All feeding will be started within 24 h of ICU admission. An EN suspension ((SP, Peptisorb), Nutricia Pharmaceuticals (Wuxi, Jiangsu, China) Co. Ltd) will be used, with a calorie content of 1 kcal/mL and a thermal nitrogen ratio of 133:1. Each bottle will contain 500 mL of nutrition preparation consisting of 61.5 g carbohydrate, 20.0 g protein, and 19.45 g fat (Wuxi). The nutritional preparations for the three groups of patients will be pumped into the nasal feeding tube through a volumetric pump (brand: Braun, origin: Melsungen AG, Germany). The treatment course will be 5 days (Table 1).

**Table 1 Tab1:** EN pumping speed scheme

Time		Continuous group	Cyclic group	Intermittent group
00:00	Pumping speed	50 ml/L		
	Check GRV	Check		
04:00	Pumping speed	50 ml/L		
	Check GRV	Check		
08:00	Pumping speed	50 ml/h	75 ml/h	150 ml/h
	Check GRV	Check	Check	Check
12:00	Pumping speed	50 ml/h	75 ml/h	150 ml/h
	Check GRV	Check	Check	Check
16:00	Pumping speed	50 ml/h	75 ml/h	
	Check GRV	Check	Check	
18:00	Pumping speed	50 ml/h	75 ml/h	150 ml/h
	Check GRV			Check
20:00	Pumping speed	50 ml/h	75 ml/h	
	Check GRV	Check	Check	
22:00	Pumping speed	50 ml/h	75 ml/h	150 ml/h
	Check GRV			Check

*GRV* Gastric residual volumes; the pumping speed will be adjusted according to GRV as follows: ≤ 250 mL, hold and recheck after 4 hours; > 250 mL: decrease to half of the original speed and recheck after 4 hours; and > 500 mL: stop and recheck after 4 h

The researchers who implement the intervention measures will receive unified training. Specialized researchers will supervise the compliance of the pumping mode by checking the execution of the doctors’ orders. Relevant concomitant care will be prohibited during the trial.

### Criteria for drop-out

The following criteria for drop-out will be used: participants (1) who cannot tolerate the nutrition preparation, resulting in diarrhea, severe abdominal distension, and other complications, and (2) who have an automatic withdrawal request submitted by either themselves or their family members at any time.

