### Outcomes

#### Primary outcome

(1) The primary outcome is the mean duration (days) of achieve the caloric goal in every group. The caloric goal of 25 kcal/kg (ideal body weight) for caloric need was calculated by a single nutritionist. The duration will be the first 5 days after the intervention.

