#### Secondary outcome

Secondary outcomes include the following: (1) the rate of onset of gastric residual (%) (defined as volume >500 mL) among the three groups; (2) abdominal pressure, (mmHg) as measured through the indirect bladder pressure, whereby the bladder urine will be emptied in the supine position, and 50 mL saline will be poured into the balloon catheter to the pubic symphysis as the base point, keeping the piezometric tube perpendicular to the ground to obtain indirect abdominal pressure; (3) the rate of onset of pneumonia in each group (%), as defined by two of the following clinical criteria, fever (> 38.3 °C) or hypothermia (≤ 36.0 °C) and leucocytosis (> 10×10^9^ cells/L) or leucopenia (≤ 4×10^9^ cells/L) and purulent tracheal aspirate or sputum. These factors are associated with the appearance of a new infiltrate or changes in the existing infiltrate on chest X-ray [11]; (4) the proportion (%) of individuals who achieve the caloric goal. The caloric goals using 25 kcal/kg (ideal body weight) for caloric need were calculated by a single nutritionist; (5) motilin levels before and 5 days after intervention; (6) the length of the ICU stay (in days) up to 12 weeks; and (7) the ICU mortality rate (%) at 28 days after intervention and survival analysis up to 12 weeks (Fig. 1). Follow-up by visit or telephone will be conducted at 28 days and 12 weeks after the intervention.

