#### Sample size

The sample size was calculated based on the duration required to achieve the caloric goal. Because there are few studies about cyclic feeding, we referred to the studies on intermittent and continuous groups. It was assumed that the time to achieve the caloric goal would be consistent with earlier RCTs [12]: 4 days (intermittent feeding group) and 3 days (continuous feeding group). Twenty-six evaluable patients per group will provide 90% power for detection at a 5% two-sided significance level. Therefore, the total sample size will be 84. Based on the sample sizes in previous studies and an estimated dropout rate extrapolated from feasibility data of 8–10% [13], we expect that 30 patients will be enrolled in each arm and that the total sample size will be at least 90.

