### Statistical analysis

All statistical analyses will be performed using SPSS 20.0 software. Measurement data will be expressed as the mean ± standard deviation. Normality tests and homogeneity tests of variance will also be performed. In cases of normal distribution and homogeneity of variance, a *t* test will be conducted; otherwise, a non-parametric test will be employed. If the measurement data conform to a normal distribution, an independent sample *t* test will be applied between two groups; one-way analysis of variance (ANOVA) will be utilized between the three groups. In the case of non-normal distribution, two groups will be compared using the Mann–Whitney *U* test, and the three groups will be compared with the Kruskal–Wallis test. Enumeration data between two and three groups will be compared using chi-square/Crosstab statistical analysis, and the results will be expressed as the frequency constituent ratio (%). *P* < 0.05 will indicate statistical significance.

For patients who die or are lost to follow-up, their observation time will be censored at the time of death or date of last contact. For patients with early withdrawal who are lost to follow-up, intention-to-treat analysis (ITT) will be applied. For the second endpoint (6), cumulative proportion survival curves according to Kaplan–Meier analysis will be obtained for each group and compared with the log-rank test. To explore the group effect on the time to the event of composite outcome, with adjustment for baseline covariates, the Cox regression model will be used.

The trial will be prematurely paused or closed by the DSMB to evaluate safety information from the study or if there is evidence of harm in the study. The principal investigator (PI) will be able to access these interim results.

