A previous study [19] has found that intermittent bolus feeding enhances muscle protein synthesis to a greater extent than continuous feeding by eliciting a pulsatile pattern of amino acid- and insulin-induced translation initiation. Moreover, it increases difficulty in moving or turning [20]. Overall, continuous pumping is not a physiological condition. Although intermittent feeding can be cost-effective for patients, it is unclear whether continuous pumping is optimal in terms of treatment effectiveness and complications. Therefore, this study will compare the effects of continuous feeding, cyclic feeding, and intermittent feeding in critically ill patients, including complications such as vomiting, diarrhea, length of stay in the ICU and increased hospitalization costs due to aspiration pneumonia. In summary, this study will reveal cyclic feeding or intermittent feeding is the optimal treatment for EN in critically ill patients and will serve as a basis for the development of EN guidelines.

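### Feed intolerance is a drop-out criterion and no rule clearly keeps these patients in the analysis, so the comparison may select on an effect of the feeding method

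*Protocol article*

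**What the plan says.** All references are to the protocol article.

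- **Criteria for drop-out.** There are two criteria. One is a withdrawal request by the patient or family. The other covers participants "who cannot tolerate the nutrition preparation, resulting in diarrhea, severe abdominal distension, and other complications".
- **Statistical analysis.** ITT is mentioned once: "For patients with early withdrawal who are lost to follow-up, intention-to-treat analysis (ITT) will be applied". The censoring rule reads: "For patients who die or are lost to follow-up, their observation time will be censored at the time of death or date of last contact".
- **Sample size.** "Twenty-six evaluable patients per group will provide 90% power". The planning values are 4 days (intermittent) and 3 days (continuous). Dropout of 8–10% is allowed for, and 30 patients per arm are to be enrolled.
- **Outcomes.** "The primary outcome is the mean duration (days) of achieve the caloric goal in every group", over the first 5 days. A secondary outcome is "the proportion (%) of individuals who achieve the caloric goal".
- **Objectives and Discussion.** A secondary objective is to "reduce the incidence of feeding complications, including the rates of onset of gastric residua and pneumonia". The Discussion promises a comparison "including complications such as vomiting, diarrhea, length of stay in the ICU".
- **Interventions and Table 1.** All three arms receive the same preparation by pump. Feeding intolerance is defined there by gastric residual volume (GRV) above 250 mL. It is managed within the trial by changing the pumping speed, or by stopping and reassessing.

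**The concern.** The arms differ only in how one product is delivered. Under randomisation, a systematic difference between arms in how often the feed is not tolerated is therefore an effect of the feeding method. Intolerance also limits the calories a patient receives, so it lies on the path to the primary outcome and to the proportion reaching goal. Diarrhea is both a named ground for drop-out and a complication the Discussion intends to compare.

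If drop-out also means leaving the analysis, the patients removed are chosen by something the assigned method caused. The arm with more intolerance would lose its worst results and look better than it is. Enrolling more patients would not correct this, because it is bias and not imprecision.

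**Working it through.** **1. Does any rule keep these patients in?** Take a patient who meets the intolerance criterion on day 2 and remains in the ICU.

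| Rule | Covers this patient? |
|---|---|
| ITT sentence | Not on its wording: it names early withdrawals who are lost to follow-up, and this patient is not lost |
| Censoring rule | No: it covers death and loss to follow-up |
| GRV rules (Interventions, Table 1) | Only if the intolerance shows as residual volume; they do not mention diarrhea or distension and say nothing on analysis |
| Follow-up at 28 days and 12 weeks | Yes for vital status and ICU stay, since no exception is made; no for the day 1–5 caloric outcome |

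No rule places this patient in the analysis of the caloric outcomes.

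**2. What does the sample size imply?** The 26 per group cannot be reproduced, because no standard deviation (SD) is stated. Solving backwards with the normal approximation:

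SD = 1 × √(26/2) / (1.960 + 1.282) = 3.606 / 3.242 = 1.11 days.

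The dropout step is 26/0.92 = 28.3 and 26/0.90 = 28.9. Both round up to 29, close to the stated 30. The margin thus fits drop-outs being planned as patients without usable data: 30 − 26 = 4 of 30 per arm.

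**3. How much could exclusion hide?** The documents give no intolerance rate by arm and no outcome for intolerant patients, so everything in this step is assumed. Suppose tolerant patients have the same mean in both arms and intolerant patients do worse by a gap *g* (days). Then

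hidden difference = *g* × (intolerance in arm A − intolerance in arm B),

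while the comparison without drop-outs shows 0.

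Reading the outcome as days at goal, with 4.0 days for tolerant and 1.0 day for intolerant patients (*g* = 3):

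- 10% vs 5%: 0.90×4 + 0.10×1 = 3.70 against 0.95×4 + 0.05×1 = 3.85, so 0.15 day is hidden.
- 20% vs 5%: 0.80×4 + 0.20×1 = 3.40 against 3.85, so 0.45 day is hidden.

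Reading it as days to goal, with tolerant patients at 3 days and intolerant patients set to the 5-day limit (*g* = 2):

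- 10% vs 5%: 2 × 0.05 = 0.10 day.
- 15% vs 5%: 3.30 against 3.10, so 0.20 day.
- 20% vs 5%: 2 × 0.15 = 0.30 day.

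The planned difference is 1 day. With equal intolerance in the arms, nothing is hidden on either reading.

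**4. Proportion reaching goal.** Assume 60% of all randomised patients reach goal in both arms and intolerant patients never do. Excluding drop-outs of 5% and 15% gives 0.60/0.95 = 63.2% and 0.60/0.85 = 70.6%. That is a spurious advantage of 7.4 percentage points for the worse-tolerated arm.

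**5. Are these rates compatible with 8–10% dropout?** A split of 20%, 5% and 5% averages (20 + 5 + 5)/3 = 10%. It fits only at the top of the range and only if every drop-out is for intolerance. A split with 10% and 5% fits without strain.

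**The case against.** The strongest reply is that the protocol nowhere excludes drop-outs from analysis. The drop-out section is silent on analysis sets, the word evaluable appears only in the sample-size paragraph, and a dropout allowance does not define an analysis set. The ITT sentence can be read as saying that even patients lost to follow-up stay in their arm, and an analysis plan that is not shown may define the sets in full. This stands as far as it goes: exclusion is an inference. But the one rule that is written does not reach these patients, and the evaluable count points the other way. If drop-out also ends collection of the day 1–5 data, no later analysis plan can recover them.

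A reader might infer that dropped patients also vanish from the ICU-stay and mortality comparisons. The text does not support that. Follow-up at 28 days and 12 weeks has no exception for patients who stop the feed, and censoring occurs only at death or last contact.

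A reader might also infer that all intolerance leads to removal. It does not. GRV-defined intolerance is managed within the trial, and a residual above 500 mL is counted as a secondary outcome. The drop-out criterion may cover a narrower group.

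Finally, the illustrated rates and gaps are assumptions, and the primary outcome can be read as days to goal or days at goal. Both objections are fair, and they limit what can be said about size.

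**Conclusion.** The point holds as a defect of wording with a plausible route to bias; it does not show that the trial will exclude these patients. The protocol makes a consequence of the assigned method a drop-out criterion and states ITT too narrowly to cover those patients. Followed as written, it could flatter the worse-tolerated arm on the primary outcome, the proportion reaching goal and the complications.

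The size is unknown. Under the assumptions shown, between 0.10 and 0.45 day of the planned 1-day difference could be hidden, and nothing if intolerance is equal across arms. The direction rests on intolerant patients doing worse than tolerant ones on these outcomes. This should be fixed, but it does not by itself invalidate the design.

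**What to change.** 1. **Criteria for drop-out.** Separate stopping the assigned feeding from leaving the study. Limit drop-out to withdrawal of consent, and continue outcome collection for everyone else. Record intolerance as an outcome.
2. **Statistical analysis.** Replace the ITT sentence with a statement that all randomised patients are analysed in the arm to which they were randomised. Any evaluable-patient analysis is supportive only.
3. **Primary outcome.** Settle the definition first, then state how these patients count. If it is days to goal, they count as not having reached goal by day 5 (for example, by worst rank). If it is days at goal, their remaining days count as zero.
4. **Consistency.** Reconcile the drop-out criterion with Interventions and Table 1, so that it is clear when intolerance is managed within the trial and when it leads to drop-out. No clinical rule is proposed here, and patient care need not change.

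The cost is rewording a few sentences and ethics committee approval of the amendment. The added data collection is small: patients are inpatients under observation during the 5-day course, and follow-up at 28 days and 12 weeks is already planned.
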